## Abstract

**Background:**

Sleeping well is an essential part of good health. Older adult populations report a high rate of sleep problems, with recent studies suggesting that cognitive processes as well as behavioral and hyperarousal-related mechanisms could be important factors in the development and maintenance of insomnia. Individuals who have an asynchronous or uncoupled sleep pattern and sleep appraisal—those who complain about their sleep but do not have poor sleep quality, and vice versa—might show differences in subjective sleep and sleep perceptions and other characteristics that could impact their treatment outcomes following cognitive behavioral therapy for insomnia (CBT-I).

**Objective:**

The purpose of this protocol is to describe the rationale and methods for a nonrandomized, single-arm trial assessing objective and subjective sleep quality in community-dwelling older adults aged 60-80 years with synchronous sleep patterns and sleep appraisal compared to those in older adults with asynchronous sleep patterns and sleep appraisal. The trial will further examine the role of cognitive, behavioral, and hyperarousal processes in mediating the treatment outcomes of web-based CBT-I.

**Methods:**

This trial aims to recruit a sample of 60 participants, who will be assigned to 1 of 4 sleep groups based on their sleep pattern and sleep appraisal status: complaining good sleepers, complaining poor sleepers, noncomplaining good sleepers, and noncomplaining poor sleepers, respectively. The trial will be completed in 2 phases: phase 1 will assess objective sleep (measured via wrist actigraphy) and subjective (self-reported) sleep. Phase 2 will investigate the impact of a web-based CBT-I program on the sleep outcomes of individuals with uncoupled sleep compared to that of individuals without uncoupled sleep, as well as the mediators of CBT-I.

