## Introduction

Sleep problems, such as insomnia, are highly prevalent in those older than 60 years of age [1], with age-related changes in sleep architecture appearing from middle age and continuing to remain relatively constant past the age of 60 years [2]. Insomnia is characterized by difficulties with sleep initiation, duration, or quality that are not due to a lack of opportunity to sleep and which results in daytime impairment [3]. It is classified as chronic when it occurs at least 3 times per week and persists for more than 3 months [4]. Furthermore, a diagnosis of insomnia consists of 2 components: sleep quality and sleep appraisal. Sleep quality can be good or poor and sleep appraisal can be characterized by the presence or absence of a sleep complaint. These 2 factors have been described as being independent of each other [5], and in about 25%-35% of individuals, sleep quality and sleep appraisal are asynchronous and uncoupled [6]. It has been proposed that such uncoupling of sleep quality and sleep complaints may be prevalent among older adults [7,8]. In their seminal study examining poor sleepers that do not complain of insomnia, Fichten et al [9] first observed the asynchrony of sleep complaints and sleep patterns in older individuals. They reported that daytime impairment, assessed as sleepiness and daytime fatigue was higher in high-distress poor sleepers than in low-distress poor sleepers, and that low-distress poor sleepers experienced the same levels of daytime impairment as good sleepers.

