The concurrent measurement of objective and subjective sleep quality will be used to determine the prevalence of individuals with asynchronous sleep patterns and sleep appraisal in this sample (phase 1). Phase 2 will assess the impact of a web-based CBT-I program on the sleep outcomes of individuals with synchronous sleep patterns and sleep appraisal and those with asynchronous sleep patterns and sleep appraisal. It is anticipated that complaining good sleepers and complaining poor sleepers will show improved sleep outcomes following CBT-I, compared with noncomplaining good and poor sleepers. We further hypothesize that individuals with a sleep complaint but without poor sleep quality (complaining good sleepers) experience higher levels of dysfunctional sleep cognitions and distress than persons with poor sleep in the absence of a sleep complaint (noncomplaining poor sleepers). We expect that additional factors such as hyperarousal [35], sleep effort [36], sleep-related self-efficacy [37], sleep locus of control [38], sleep-related behaviors [39], and chronotype [40] mediate the relationship between web-based CBT-I and sleep outcomes in older adults; therefore, these processes will also be examined.

Since our planned study is likely to generate a considerable amount of data, we aim to reduce publication bias and improve the reproducibility of our research by publishing this research protocol.

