Participants will wear an actigraph and complete a sleep diary over 96 hours (72 hours plus an additional 24 hours to account for nonadherence wear time). Actigraphic sleep assessment will assess sleep onset latency, wake-after-sleep onset, total sleep time, and the number of nighttime awakenings. The Actigraph model wGT3X-BT activity monitor (ActiGraph) will be used. Actigraphy has been recognized by the American Academy of Sleep Medicine as an appropriate method for assessing sleep. However, when compared with polysomnography, actigraphy has lower accuracy in detecting wake periods; especially in individuals with poor sleep quality [50]. The actigraphy data will be manually scored along with a sleep diary. This process was recommended by Boyne et al [51] to optimize agreement with polysomnography-measured sleep-wake. Additionally, the Choi algorithm will be used to differentiate between wear and nonwear times, which more accurately estimates time spent sedentary than other algorithms [52]. The sleep diary is a modified version of the Consensus Sleep Diary [53], which, in addition to the questions covered by the Consensus Sleep Diary, records the total duration of all daytime naps, how many times the study participant got up during the night, what time they had planned to wake up at, and whether they took any sleep medication.

Participants will be grouped into 4 sleep groups: noncomplaining good sleepers, complaining good sleepers, noncomplaining poor sleepers, and complaining poor sleepers. Participants will be grouped based on their actigraphy results and sleep complaint status (complaining versus noncomplaining sleepers), with participants appraised as poor sleepers if their sleep onset latency or wake-after-sleep onset is ≥31 minutes, 3 times or more during the recording period (as per actigraph recording). A participant will be considered a complaining sleeper if they report having had a sleep problem (eg, trouble falling asleep) for a minimum of 6 months at baseline data collection [5,54].

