### Statistical Analysis

An a priori power analysis using the program G*Power was performed to assess whether the study will have enough power to detect significant differences in sleep outcomes between the study groups [60]. We calculated that a sample size of 40 would be sufficient to detect this size effect. In order to account for attrition rates and missing data, a minimum of 60 participants will be recruited for the study.

Since sleep complaint status (sleep problem, eg, initial insomnia, for a minimum of 6 months) is used to classify participants as complaining or noncomplaining sleepers, multivariate ANOVA will be conducted separately to examine subjective and objective sleep quality for the 4 sleep groups. The multivariate ANOVA enables the analysis of multiple continuous dependent variables simultaneously (eg, sleep onset latency, wake-after-sleep onset, total sleep time, and the number of nighttime awakenings). In addition, a mediation analysis will be performed to determine whether sleep improvements following web-based CBT-I are the result of changes in sleep-related beliefs or other factors in older adults living in the community. Mediation analysis will be carried out using the bootstrapping method in the Hayes Process Macro for mediation, moderation, and conditional analysis for SPSS (version 28.0; IBM Corp) [61,62].

Actigraphy measures will be scored using the Cole-Kripke algorithm, which is suitable for use with older populations [63] and using ActiLife software (ActiLife 6 software, Version 6.13.1, ActiGraph). The autoscored data will be manually compared with the sleep diary to determine any incongruence between the actigraph measurements and the sleep diary.

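### Phase 2 is framed as uncoupled versus coupled sleepers (an interaction), but its hypothesis is complaining versus noncomplaining sleepers (a main effect), and no contrast is named

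*Protocol article*

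**What the plan says.** The abstract (Background) describes uncoupled sleepers as "those who complain about their sleep but do not have poor sleep quality, and vice versa". With the four groups written as CG (complaining good), CP (complaining poor), NG (noncomplaining good) and NP (noncomplaining poor), uncoupled is CG + NP and coupled is CP + NG.

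The abstract (Methods) gives the phase 2 comparison as "the sleep outcomes of individuals with uncoupled sleep compared to that of individuals without uncoupled sleep". The last part of the Introduction restates the phase 2 populations as "individuals with synchronous sleep patterns and sleep appraisal and those with asynchronous sleep patterns and sleep appraisal", and the abstract's Objective frames the trial in the same terms.

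The next sentence of the Introduction gives the only directional prediction about treatment outcome: "complaining good sleepers and complaining poor sleepers will show improved sleep outcomes following CBT-I, compared with noncomplaining good and poor sleepers". It gives no magnitudes, and does not say that the two complaining groups, or the two noncomplaining groups, change equally.

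The Statistical Analysis section says that "multivariate ANOVA will be conducted separately to examine subjective and objective sleep quality for the 4 sleep groups". It names no contrast among those groups. Group sizes are not set by design: "Participants will be grouped based on their actigraphy results and sleep complaint status".

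**The concern.** The aim and the hypothesis stand in adjacent sentences and pair the same four groups differently. The aim sets CG + NP against CP + NG. The hypothesis sets CG + CP against NG + NP. Each side of the aim's comparison therefore holds one group expected to improve more and one expected to improve less.

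What is at stake is how the phase 2 result is read. An uncoupled-coupled comparison could show no difference, or a difference in either direction, while the hypothesis is true. It cannot serve as the test of that hypothesis. The omnibus four-group test does not fill the gap, because a significant result does not say which groups differ or in which direction.

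**Working it through.** **Inputs.** The group definitions, the phase 2 comparison and the hypothesis are taken from the abstract and Introduction. The calculated sample size of 40 and the recruitment target of 60 are from Statistical Analysis. The sample size of 40 cannot be reproduced, since the article gives no effect size, alpha, power or test family ("We calculated that a sample size of 40 would be sufficient to detect this size effect"). The contrast argument does not depend on it. Assumed here: the sizes of the gains, the group mixes, alpha 0.05, and a complaint effect of 0.8 SD for the power check.

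**Step 1: the two contrasts.** Let a, b, c, d be the mean improvements in CG, CP, NG, NP.

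- Aim (uncoupled − coupled): (a + d)/2 − (b + c)/2 = [(a − c) − (b − d)]/2. This is half the difference between the complaint effect in good sleepers (a − c) and in poor sleepers (b − d), i.e. the interaction.
- Hypothesis (complaining − noncomplaining): (a + b)/2 − (c + d)/2, i.e. the main effect of complaint.
- The weights, in the order CG, CP, NG, NP, are (½, −½, −½, ½) and (½, ½, −½, −½). Their product sum is ¼ − ¼ + ¼ − ¼ = 0, so with equally weighted cells the contrasts are orthogonal.

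**Step 2: equal complaint effect.** Take a = b = D and c = d = 0. The aim's contrast is (D + 0)/2 − (D + 0)/2 = 0. The hypothesis contrast is (D + D)/2 − 0 = D.

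**Step 3: unequal gains that still satisfy the hypothesis, equal group sizes, larger gain = 1.**

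| CG | CP | NG | NP | Uncoupled − coupled | Complaining − noncomplaining |
|---|---|---|---|---|---|
| 0.5 | 1 | 0 | 0 | 0.25 − 0.50 = −0.25 | 0.75 |
| 1 | 0.5 | 0 | 0 | 0.50 − 0.25 = +0.25 | 0.75 |

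The hypothesis holds in both rows, and the aim's contrast changes sign.

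**Step 4: pooling people instead of weighting cells equally.** With CG = CP = D and NG = NP = 0, the pooled difference is D × [nCG/(nCG + nNP) − nCP/(nCP + nNG)]. The Introduction gives a background figure that "in about 25%-35% of individuals, sleep quality and sleep appraisal are asynchronous and uncoupled", which is 15 to 21 of 60 (0.25 × 60 and 0.35 × 60). The mixes below have 18 or 20 uncoupled sleepers among 60. The split within each pool is assumed.

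| CG/CP/NG/NP | Pooled uncoupled − coupled |
|---|---|
| 10/20/20/10 | 10/20 − 20/40 = 0 |
| 12/24/18/6 | 12/18 − 24/42 = +0.10 D |
| 15/20/20/5 | 15/20 − 20/40 = +0.25 D |
| 5/20/20/15 | 5/20 − 20/40 = −0.25 D |

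The same complaint effect thus appears as no difference, a benefit or a deficit for uncoupled sleepers, depending on a mix that the design does not control.

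**Step 5: omnibus test versus the one-degree-of-freedom contrast.** For one outcome in four equal groups with a complaint effect of 0.8 SD and no other differences, the group means lie 0.4 SD either side of the overall mean. Then f = 0.4, and the noncentrality is N × 0.4² = 6.4 at N = 40 and 9.6 at N = 60. The denominator degrees of freedom are N − 4.

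| N | Omnibus test, 3 df | Complaint contrast, 1 df |
|---|---|---|
| 40 | 0.50 | 0.69 |
| 60 | 0.71 | 0.86 |

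This is a univariate illustration, not the power of the planned multivariate test.

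**The case against.** The strongest reply is that the stated group analysis keeps all four groups. No section says CG and NP will be pooled and tested against CP and NG, so a complaint effect would not cancel in the analysis described. That stands. The pooled figures in step 4 show what the abstract's comparison would give if taken literally, not what the plan says will be run.

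A reader might go further and infer that the stated comparison must have expected value zero whenever the hypothesis is true. The document does not support that. It needs an equal complaint effect in good and poor sleepers, together with equal cell weights or proportionate group sizes, and the article states neither. Equal gains are also doubtful on the actigraphic outcomes. The Design section defines poor sleepers by long sleep onset latency or wake-after-sleep onset, so complaining good sleepers may have less room to improve on those measures than complaining poor sleepers. That argues against a zero but does not rescue the comparison: the first row of step 3 has this pattern, and there uncoupled sleepers look worse although the hypothesis holds.

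A reader might also infer that phase 2 has no question its data can answer. That is too strong as well. The Introduction makes a directional prediction, and four-group data can contradict it. An interest in coupled and uncoupled sleepers is compatible with expecting complaint status to drive response.

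Finally, contrast coding is often left to a full analysis plan, which is not shown. That is fair for the coding. It does not cover the disagreement between aim and hypothesis, which is in the article's own text.

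**Conclusion.** The concern holds as a misalignment of moderate weight. The phase 2 comparison is the complaint by sleep-quality interaction, the hypothesis is the complaint main effect, and the four-group test names neither.

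The orthogonality is algebra and needs only equal cell weights. The zero result needs, in addition, an equal complaint effect across sleep-quality strata. Without that, the hypothesis determines neither the sign nor the size of the uncoupled-coupled contrast. The gain from naming the contrast, about 0.15 in power at 60 participants (0.86 − 0.71) and 0.19 at 40 (0.69 − 0.50), rests on the assumed 0.8 SD effect, balanced groups and a single outcome. Because the described analysis retains all four groups, the information needed to test the hypothesis is not lost, and the point falls short of a flaw that must be cured before the trial can be interpreted.

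**What to change.** - Analyse change in each sleep outcome in a 2×2 model with complaint status and sleep quality as factors.
- Test the Introduction's hypothesis with the complaint main-effect contrast, weighting the cells equally.
- Report uncoupled versus coupled as the interaction contrast, with its own estimate and interval.
- State which contrast is primary. That is the sponsor's choice: keeping the uncoupled-coupled question primary is coherent if the hypothesis is rewritten to match.
- Align the abstract's Objective and Methods and the Introduction with that choice.

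The cost is a few sentences and one contrast statement, with no new data. Since the article reports the phase 2 analysis as finalized in July 2022, the practical step is to report both contrasts, correctly labelled, and to disclose that the article designated neither as the test of the hypothesis.

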**Results:**

Recruitment began in March 2020, and the last participants were recruited by March 2021. A total of 65 participants completed phases 1 and 2. Data analysis for phase 1 was finished in December 2021, and data analysis for phase 2 was finalized in July 2022. The results for phase 1 were submitted for publication in March 2022, and those for phase 2 will be submitted by the end of December 2022.

**Conclusions:**

This trial will provide guidance on factors that contribute to the variability of sleep in older adults and their sleep outcomes following CBT-I. The outcomes of this study could be valuable for future research attempting to tailor CBT-I to individual needs.

**Trial Registration:**

Australian New Zealand Clinical Trials Registry ACTRN12619001509156; https://tinyurl.com/69hhdu2w

**International Registered Report Identifier (IRRID):**

DERR1-10.2196/32705

## Introduction

Sleep problems, such as insomnia, are highly prevalent in those older than 60 years of age [1], with age-related changes in sleep architecture appearing from middle age and continuing to remain relatively constant past the age of 60 years [2]. Insomnia is characterized by difficulties with sleep initiation, duration, or quality that are not due to a lack of opportunity to sleep and which results in daytime impairment [3]. It is classified as chronic when it occurs at least 3 times per week and persists for more than 3 months [4]. Furthermore, a diagnosis of insomnia consists of 2 components: sleep quality and sleep appraisal. Sleep quality can be good or poor and sleep appraisal can be characterized by the presence or absence of a sleep complaint. These 2 factors have been described as being independent of each other [5], and in about 25%-35% of individuals, sleep quality and sleep appraisal are asynchronous and uncoupled [6]. It has been proposed that such uncoupling of sleep quality and sleep complaints may be prevalent among older adults [7,8]. In their seminal study examining poor sleepers that do not complain of insomnia, Fichten et al [9] first observed the asynchrony of sleep complaints and sleep patterns in older individuals. They reported that daytime impairment, assessed as sleepiness and daytime fatigue was higher in high-distress poor sleepers than in low-distress poor sleepers, and that low-distress poor sleepers experienced the same levels of daytime impairment as good sleepers.

The distinction between high- and low-distress, or asynchronous, good and poor sleepers could also be relevant for the treatment of sleep problems, as it could signify differences in how individuals respond to insomnia treatment. Cognitive behavioral therapy for insomnia (CBT-I) is the recommended first-line treatment method to address insomnia in any age group [10]. It contains several core components such as psychoeducation, cognitive therapy, and behavior therapy [11,12]. However, despite a widespread recommendation for the use of CBT in the treatment of insomnia, the provision of pharmacotherapy remains the dominant approach to address sleep problems in older adults. This is in part due to a lack of trained clinicians [13]. The pharmaceutical treatment of insomnia can lead to polypharmacy, the concurrent use of multiple medicines, which is an identified issue for older individuals [14]. Polypharmacy can result in interaction effects or side effects, for example, an increased fall risk, in older adults [15,16]. CBT-I’s effectiveness and safety on the other hand have been well established, demonstrating moderate to large effects on improving sleep continuity [17]. CBT-I is also an effective treatment option for older adults, with recent research suggesting that even brief interventions can improve sleep onset latency, wake-after-sleep onset, sleep efficiency, and sleep quality [18,19], making it a viable alternative for older individuals at risk of polypharmacy.

The exact mechanisms by which such improvements are achieved remain unknown, and it is not fully understood why some individuals respond to CBT-I and others do not. It is estimated that 20%-30% of individuals with insomnia do not have a treatment response to CBT-I [20]. Cognitive processes are important factors in the development and maintenance of insomnia [5,20-27], particularly in older adults [28-30]. Discrepancies in subjective sleep perception and objectively measured sleep are also common [31]. In order to scrutinize sleep quality in older adults and the role that dysfunctional beliefs and other cognitive or behavioral factors play in mediating the outcomes of CBT-I, this study will examine both subjective and objective sleep quality in older adults aged 60-80 years in Western Australia. The age category of 60 years and older has been selected as it is the United Nations’ agreed cutoff for the classification of older persons in high-income nations [32]. The upper cutoff of 80 years was chosen based on an American Academy of Sleep Medicine report highlighting that the sleep variability in adults aged 80 years and older is either significantly higher or significantly lower than that in adults under 65 years [33,34]. Consequently, adults aged older than 80 years will be excluded.

The concurrent measurement of objective and subjective sleep quality will be used to determine the prevalence of individuals with asynchronous sleep patterns and sleep appraisal in this sample (phase 1). Phase 2 will assess the impact of a web-based CBT-I program on the sleep outcomes of individuals with synchronous sleep patterns and sleep appraisal and those with asynchronous sleep patterns and sleep appraisal. It is anticipated that complaining good sleepers and complaining poor sleepers will show improved sleep outcomes following CBT-I, compared with noncomplaining good and poor sleepers. We further hypothesize that individuals with a sleep complaint but without poor sleep quality (complaining good sleepers) experience higher levels of dysfunctional sleep cognitions and distress than persons with poor sleep in the absence of a sleep complaint (noncomplaining poor sleepers). We expect that additional factors such as hyperarousal [35], sleep effort [36], sleep-related self-efficacy [37], sleep locus of control [38], sleep-related behaviors [39], and chronotype [40] mediate the relationship between web-based CBT-I and sleep outcomes in older adults; therefore, these processes will also be examined.

Since our planned study is likely to generate a considerable amount of data, we aim to reduce publication bias and improve the reproducibility of our research by publishing this research protocol.

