### Recruitment

Older adults with and those without self-reported poor sleep will be recruited from the community in Western Australia, with advertisements being displayed on the Sleep Health Foundation website and social media sites such as Facebook, as well as in community centers and senior citizen organizations. Participants are eligible to take part if they are aged 60-80 years and ordinarily reside in Western Australia, if they have not been diagnosed with an existing sleep disorder other than insomnia, if they have not been diagnosed with a severe psychiatric or cognitive disorder, if they have not engaged in regular shift work in the past year, and if they have not been diagnosed with epilepsy or are at high risk of falling.

Screening for the presence of obstructive sleep apnea, which is common among older adults, will be conducted using the STOP-Bang (snoring, tiredness, observed apnea, high BP, BMI, age, neck circumference, and male gender) questionnaire, a brief self-report instrument [41]. The STOP-Bang questionnaire has demonstrated a high sensitivity of 84% in detecting obstructive sleep apnea [41]. Participants that score 0 to 2 on the instrument are considered unlikely to present with moderate to severe sleep apnea. Participants who took sleep medication were not excluded, as CBT-I has shown to be effective in those who take sleep medication [12]. However, the type, dosage, and frequency of any medication taken by participants were recorded as part of the demographic assessment.

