Following the baseline assessment, including the recording of demographic information and sleep complaints, the administration of the questionnaires, and actigraphy measurement, all groups will receive identical instructions for the web-based CBT-I program. Participants will be required to complete the 4 sessions plus homework of the program within 4 weeks. Participants will receive weekly email reminders from the principal investigator to confirm the completion of each of the 4 CBT-I modules. Once the completion of the CBT-I program has been confirmed with the participant, actigraphy, sleep diary, and questionnaire measurements will be repeated posttreatment. The study process is shown in Figure 1.

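### Phase 2 comparisons between actigraphy-defined good and poor sleepers, including the four-group test, may not be separable from regression to the mean or from the baseline difference

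*Protocol article*

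**What the plan says.** The Objective in the abstract describes a "nonrandomized, single-arm trial assessing objective and subjective sleep quality in community-dwelling older adults aged 60-80 years", and under Procedure "all groups will receive identical instructions for the web-based CBT-I program". No group goes untreated.

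Under Design, sleep pattern is set by baseline actigraphy, with "participants appraised as poor sleepers if their sleep onset latency or wake-after-sleep onset is ≥31 minutes, 3 times or more during the recording period". The recording lasts 96 hours, one day of which is a reserve for non-wear, so it gives three or four nights. Complaint status is set separately, by a self-reported sleep problem of at least 6 months. Procedure has the actigraphy, diary and questionnaires repeated once after the programme.

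For phase 2 the Introduction expects that "complaining good sleepers and complaining poor sleepers will show improved sleep outcomes following CBT-I, compared with noncomplaining good and poor sleepers". The abstract gives the subject of this phase as "the impact of a web-based CBT-I program on the sleep outcomes of individuals with uncoupled sleep compared to that of individuals without uncoupled sleep".

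Statistical Analysis names one group analysis: "multivariate ANOVA will be conducted separately to examine subjective and objective sleep quality for the 4 sleep groups". SOL and WASO are among its example dependent variables. The section mentions no time factor, change score or baseline covariate.

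**The concern.** The variables that sort participants into good and poor sleepers are also phase 2 outcomes, and the recording used for sorting is also the baseline. Three or four nights of WASO measure a person's usual WASO with error. Some participants are labelled poor because those nights were unusually bad, and some good because they were unusually quiet. On re-measurement both groups drift towards their usual level with no treatment effect at all.

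The named MANOVA can be applied to phase 2 in two ways, and each has a problem. On change scores it picks up this drift. On post-treatment values it largely reproduces the difference by which the groups were formed. With no control arm, nothing in the data exposes either artefact. What is at stake is the statement of who benefits from CBT-I, wherever it rests on comparing good with poor sleepers or on the four-group test.

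**Working it through.** **Inputs from the article.** Poor = SOL or WASO of 31 min or more on at least 3 occasions; about 4 nights (96 h / 24 h); the same recording repeated after treatment; at least 60 recruited. The article's own planning figure (40, raised to 60) comes without effect size, power or test, so it cannot be reproduced. Only N = 60 is used here.

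**Assumed inputs (not in the article).** Nightly WASO log-normal, median 30 min, coefficient of variation 0.6; night-to-night intraclass correlation (ICC) 0.3, 0.5 or 0.7; poor = at least 3 of 4 nights at 31 min or more; treatment effect zero. Only WASO is modelled, although the rule also admits SOL.

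**Step 1: expected shrinkage.** Reliability of a 4-night mean (log scale) = 4·ICC / (1 + 3·ICC).
- ICC 0.3: 1.2 / 1.9 = 0.63
- ICC 0.5: 2.0 / 2.5 = 0.80
- ICC 0.7: 2.8 / 3.1 = 0.90

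About 37%, 20% and 10% of the baseline good/poor gap should therefore disappear on re-measurement by chance alone.

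**Step 2: null simulation, poor versus good, change in mean WASO.** The last two columns are rejection rates of an unadjusted 5% test of change at N = 60. Differences were taken before rounding.

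| ICC | Poor (min) | Good (min) | Difference (min) | Difference (SD) | Poor vs good | Complaining vs noncomplaining |
|---|---|---|---|---|---|---|
| 0.3 | -4.8 | +2.5 | -7.4 | -0.58 | 49% | 5% |
| 0.5 | -2.9 | +1.8 | -4.7 | -0.43 | 30% | 6% |
| 0.7 | -1.6 | +1.0 | -2.6 | -0.30 | 17% | 5% |

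**Step 3: sensitivity to the assumptions.** With medians of 25-32 min and the same ICC range, poor-versus-good change tests rejected in 21-59% of null trials and four-group change tests in 16-52%. One further set of runs (median 32 min, log-SD 0.6) gave 71%, 46% and 26%. Roughly 15-70% covers all of these, and 71% is the outer end. Four-group tests on post values rejected in 91-100%, because they recover the baseline difference.

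**Step 4: baseline adjustment, poor versus good.** Regressing the log post value on group and log baseline value brings the group coefficient to about 0 and rejection to 4-6%.

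**Step 5: the complaint contrast.**
- *Actigraphy, change.* The mean difference is within 0.05 min of zero and rejection is about 5%, because good and poor sleepers sit on both sides.
- *Actigraphy, baseline-adjusted.* Rejection rises to 7-17%, against complainers.
- *Questionnaire, change* (assumed reliability 0.7-0.85). The spurious difference is 0 SD if complaint status is unrelated to transient baseline error, and -0.06 to -0.27 SD if the correlation is 0.1-0.3.
- *Questionnaire, baseline-adjusted.* The null usually shifts the other way: +0.07 to +0.36 SD for correlations of 0 to 0.2, and +0.12 to -0.02 SD at 0.3.

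**The case against.** The strongest objection is that the article's hypothesis concerns complaint status, not sleep pattern. Complaint rests on a 6-month history rather than a cut on nightly actigraphy. A reader might infer that regression to the mean will appear as the hypothesised benefit for complainers. The documents do not support that: step 5 shows essentially no actigraphic bias in this contrast. For the two asynchronous groups the drift even runs against the prediction. With ICC 0.5 and complaint modestly related to true WASO, complaining good sleepers change by +2.2 min and noncomplaining poor sleepers by -3.4 min. The uncoupled-versus-coupled contrast also has good and poor sleepers on both sides, which dilutes the artefact. This objection stands, and it limits the point to comparisons across the good/poor line and to the four-group test.

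Second, the MANOVA sentence may have been written for phase 1, and an unseen analysis plan may hold a baseline-adjusted phase 2 model. That is fair: the absence of adjustment is read from what the article names. But this is the only group analysis it names, phase 2 makes a group comparison, and the grouping rule and single-arm design are fixed in the article whatever another document adds.

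Third, a reader might also fault the plan for leaving sleep medication out of the model, since "the type, dosage, and frequency of any medication taken by participants were recorded as part of the demographic assessment". That is detail an article may leave to the analysis plan, and it forms no part of this point.

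Fourth, the lack of a control arm is openly declared. That is true of the design, but the stated aim of assessing impact claims more than the design can carry.

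**Conclusion.** The point holds for phase 2 actigraphic comparisons between good and poor sleepers and for the four-group test. With zero treatment effect, and under assumed distributions and reliabilities, tests of change reject in roughly 15-70% of trials and four-group tests of post values in 91-100%. The direction is firm because it follows from the grouping rule. The size is not firm, because the article gives neither a WASO distribution nor a night-to-night reliability.

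It does not hold for complaining versus noncomplaining sleepers on actigraphy (about 5%). On questionnaires a bias is possible but depends on an unknown: how far the reported complaint follows transient baseline scores. It would also be too strong to say that baseline adjustment cures everything. It removes the good/poor artefact but can bias the complaint contrast the opposite way, since those groups differ before treatment. Whichever contrast is used, a single-arm design cannot attribute a group difference in change to CBT-I.

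**What to change.** 1. For each phase 2 actigraphic outcome, fit the post-treatment value on sleep pattern, complaint status and their interaction, with the baseline value of that outcome as covariate. A log scale suits SOL and WASO if they are skewed.
2. Do not interpret raw post-treatment or change differences between good and poor sleepers.
3. For complaining versus noncomplaining sleepers, report the change-score and the baseline-adjusted estimates side by side, and say that they can err in opposite directions.
4. Describe pre-post change as uncontrolled, and replace the language of CBT-I impact with association, or change following CBT-I.

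Cost: all the data needed are already collected. The article reports the phase 2 analysis as finished, so this means some re-analysis and rewording, one error degree of freedom per model for the baseline term, and a more modest conclusion.
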